### Methods in analysis to handle protocol non-adherence and any statistical methods to handle missing data {20c}

We will measure non-adherence to the random assignment and to the implementation of the curriculum thanks to the different data collected over the course of the school year. As we estimate intention-to-treat effects, we respect the initial random assignment of the teachers to the treatment or the control groups, whatever of the adherence status to the initial assignment or the implementation fidelity.

In the Lasso regressions and in the final regressions where the effects of the treatment is estimated, missing values of the control variables will be replaced by the mean of these controls, and for each control, an indicator for observations for which the control is missing will be included in the regression. We will not impute missing values for outcome variables.

### Plans to give access to the full protocol, participant-level data, and statistical code {31c}

We will publish the full protocol, anonymous data, and related statistical codes used to analyze the data and estimate the effects of the curriculum on the different outcomes.

## Oversight and monitoring

### Composition of the coordinating center and trial steering committee {5d}

Data monitoring is carried out by principal investigators: they ensure progress of research protocol, randomization, data collection, and visit organization. A research assistant helps principal investigators in corresponding with teachers and evaluators and conducts administrative tasks relative to trial (e.g., teacher and evaluator remuneration, material purchase, and preparation). Data analysis and statistics are carried out by one of the principal investigators [OC], with the help of an expert statistician from the J-PAL ([QD], Abdul Latif Jameel Poverty Action Lab). Another research assistant helps principal investigators with evaluators’ training course. Evaluators are supervised by a principal investigator during the 3-day training and evaluation and are regularly in contact by phone and emails with principal investigator during visit periods. Principal investigators meet regularly to ensure and control trial progress and are in constant contact by emails.

### Composition of the data monitoring committee, its role, and reporting structure {21a}

An independent data monitoring committee has not been formed and no independent auditing will take place.

### Adverse event reporting and harms {22}

Due to the intervention nature, serious adverse events are not expected. Any adverse event that occurred will be reported in the manuscript describing trial results if they are directly related to intervention. Those adverse events will be monitored by principal investigators and addressed until resolution.

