### Implementation {16c}

One of the principal investigators [TV] generated the allocation sequence, enrolled teachers, and assigned teachers to interventions.

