Description of the tools used and variables retained:School performanceIndicators of school performance are obtained 2 years after the beginning of the intervention, based on national evaluations taking place in the first and second years of primary school in France (*EVALAIDE* in Grade 1 and Grade 2). These evaluations target various literacy and math skills: reading out loud words, reading out loud text, understanding phrases while reading them, writing syllables, writing words, operating phonemes, recognizing letters, comparing letters, knowing letters’ names and sounds, understanding words, understanding phrases, understanding texts, reading numbers, writing numbers, visualizing numbers, comparing numbers, ordering numbers in sequence, resolving math problems, calculating mentally, adding numbers, subtracting numbers, and reproducing geometrical forms. *Mathematic skills, Reading skills*: based on these tests, we will create two outcomes corresponding to mathematics and reading skills.Standardized observations*Individualized Classroom Assessment Scoring System (InCLASS):* The InCLASS is a standardized naturalistic observation tool analyzing 3 to 5 years old children’s interactions in a classroom context [34]. It comprises 10 dimensions: (1) positive engagement with the teacher (which comprises the following indicators: attunement to the teacher, proximity seeking, and shared positive affect with teacher), (2) communication with the teacher (conversation initiated and maintained with the teacher, and variety of speech with the teacher), (3) teacher conflict (aggression, negative affect, attention-seeking behaviors, and non-compliance toward the teacher), (4) peer sociability (proximity seeking, shared positive affect, cooperation toward peers, and popularity), (5) peer communication (conversation initiated and maintained with peers, and variety of speech with peers), (6) peer assertiveness (positive initiation of interactions with peers and leadership toward peers), (7) peer conflict (aggression, negative affect, attention-seeking and confrontation toward peers), (8) engagement with tasks (sustained attention and active engagement in classroom activities), (9) self-reliance (personal initiative and independence in classroom activities), and (10) behavior control (patience, activity level matching expectations, and physical awareness) [13]. These dimensions have been grouped into four domains in a previous study using confirmatory factor analyses [13]: positive engagement with teachers (grouping positive engagement and communication with teacher), positive engagement with peers (peer sociability, peer communication, and peer assertiveness), positive engagement with tasks (engagement with tasks and self-reliance), and negative classroom engagement (teacher conflict, peer conflict, and the reversed score of behavior control). This tool has demonstrated solid inter-rater reliability, construct validity, and criterion validity [34]. *Positive engagement with teachers score, Positive engagement with peers score, Positive engagement with tasks score, Negative classroom engagement score:* Each dimension is rated on a 7-point scale, with higher score indicating higher frequency and/or quality of behavior within a dimension. Data from each of the observation cycles—collected by each data collector—are averaged to obtain final dimension scores. Mean score for the four domains are then calculated by averaging final dimensions scores within each of the four domains. Inter-rater agreement is calculated based on 12.5% of all observations, where the two data collectors independently observe the same child.Tasks*Challenging Situations task (CST):* An app-version of the full CST task is used to assess children’s emotional response in challenging interpersonal problems and ability to solve interpersonal problems [28]). Situation, emotion vignettes, and behavioral response vignettes are displayed on a tablet and responses are automatically registered. Emotional responses are composed of four different choices: happy, indifferent (“just ok”), sad, and angry. Behavioral responses are composed of four types of choices: a prosocial choice, an aggressive choice, an avoidant choice, and a dysregulated (“crying”) choice [27]. Examiners describe each situation picture and ask what the child would do in such a situation, by presenting response picture choices and asking the child to point at the picture corresponding to their emotion/behavior when/if the situation happens. Previous studies suggested that choosing sad emotion and prosocial behaviors on the CST constitutes adaptive behaviors that are linked with emotion knowledge and peer acceptance [28], and predicts classroom adjustment, pre-academic literacy skills, kindergarten readiness and academic achievement [26, 27, 81]. On the opposite, choosing aggressive response is associated with poor peer acceptance [28], poor classroom adjustment, and poor academic readiness [27]. *Adaptive responses score, Aggressive behavior score:* Along with previous studies [26, 81], the proportion of adaptive responses (Sad emotion + Prosocial behavior” responses) and aggressive behavior responses across the six vignettes (ranging from 0 to 6) are calculated.*Emotion matching task-expressive knowledge:* The expressive knowledge sub-task of the Emotional Matching Task (EMT) measures 3 to 6- years-old children expressive emotion knowledge – i.e., the ability to recognize and label expressions of others’ emotions (based on Izard test [46, 55];). A sample of 12 colored photographs representing ethnically-diverse children with emotional facial expression are presented on a tablet screen: happiness, sadness, fear/surprise, anger, and mixed (anger/sadness). Children are asked each time what the child on the picture is feeling [55]. The EMT has demonstrated good criterion validity, strong reliability and construct validity [55], and preliminary evidence for cross-cultural validity has been found [3]. *Expressive emotional knowledge score:* Each child verbal responses are assigned to a score of 0 (= incorrect response), 1 (=accepted response), or 2 (=correct response). Accepted verbal responses are pre-determined and listed in a table before test sessions using the instruction manual. All items are summed to obtain the total score, with higher score indicating better expressive emotion knowledge.*Executive functioning battery:* We use an app-version of the EF battery (“*EF Touch*”), a battery of six EF tasks designed for preschool children from 3 to 5 years, which was found to show good criterion validity [83]. Each response is automatically registered on a computer communicating with the tablet. Analyses of dimensionality show that performance on EF tasks is best characterized by a single EF factor [83]. The Houses, Pick the Picture and Something the Same tasks, when combined, best approximate an EF latent variable underlying performance on all the six tasks [84]. We therefore selected these three tasks to assess children’s EF within a single EF latent factor model. Finally, following the suggestion of Willoughby et al. [84], only two randomly selected tasks out of three are administered to each child using a planned missing design, in order not to overload attention capacities of children and to reduce global test burden. Score for the missing parameter is estimated through an imputation procedure.*Houses game (also named Working Memory Span game):* This task assesses working memory span. Children are presented with houses in which are located a line-drawing animal and a color dot. They are asked to name both the animals and the colors in each of the houses. Then, animals and color dots disappear from houses. Children have to recall either which animal *or* which color was in the target house, thus holding in mind two pieces of information and activating one of them (i.e., animal name) while overcoming interferences from the other (i.e., color name) [84]. Task becomes increasingly difficult as the number of houses on the screen increases (from one to three houses).*Pick the Picture (PTP) game:* This is a self-ordered pointing task assessing working memory. In this task, children are asked to touch once each picture appearing on the screen, so that all of the pictures “get a turn” [84]. Between each touch, location of pictures is changed in a randomized order. Difficulty of the task increases as the number of pictures increases (from two to six pictures).*Something’s the Same (STS) game:* This task evaluates cognitive flexibility. For each item, children are asked to shift their attention from one dimension of similarity to another dimension of similarity [84]. Initially, they are presented with two pictures that share one dimension of similarity (e.g., color, shape, size, etc.). Then, a third picture is presented, and children have to tell how this new picture is similar to one of the original pictures. This last picture always shares a different dimension of similarity with one of the original pictures. In the second part of the game, all pictures are presented at once and children have to identify two different dimensions of similarity.*Working memory span score 1 (Houses), Working memory span score 2 (Pick the picture), Cognitive Flexibility Score*: for each EF battery game, each response is coded into a dichotomous variable (0 = incorrect response, 1 = correct response). The total score is a proportion ranging from 0 to 1, with 0 indicating no items correct and 1 indicating all items are correct.*Peer acceptance task:* The peer acceptance task measures how a particular child is accepted and liked by his peers in his/her class. It is a peer rating measure inspired by Asher et al. (1979) sociometric procedure [14]. Children are presented with photos of their classmates. After identifying classmates on these photos, they are asked to sort each photo of classmates into three envelopes: happy smiley for “I really like to play with this child”; neutral smiley for “I kind of like to play with this child”; unhappy smiley for “I don’t like to play with this child”. Answers are coded 3, 2, and 1 respectively. This procedure shows adequate reliability and validity [14]. *Peer acceptance score*: After testing each child, we assess how many times a child photo is put in each envelope: a mean score is calculated by summing up the score on each trial and dividing by the number of children in the classroom minus one. The final score indicates how much a child is accepted by his peers, with higher scores indicating higher levels of acceptance.*Sharing task:* This task evaluates child sharing. The sharing task used in this study is a sub-section of the task designed by Flook et al. [38], divided into two trials. For each trial, children are presented with 10 stickers. They are told that they can keep as many stickers as they want for themselves and share as many as they want with another child. They then separate stickers between two different envelopes (identified with the photo of the assessed child and the photo of the other child). In the first trial, the other child is the one identified by the assessed child as his/her most-liked classmate, and in the second trial, the other child is the one identified as the least-liked classmate. Sharing ability has been shown to differ between groups that received an SEL intervention compared to control group [38]. *Sharing proneness score*: 20 minus the total number of stickers (ranging from 0 to 20) put in the “me” envelope across the two trials is calculated. Higher scores indicate higher levels of sharing tendencies.Teacher-rated questionnaires*Commitment to implement:* Teachers in the intervention group are asked about their commitment to implement the program using a single item: “I feel motivated to use the program/strategies in my classroom”. Previous study indicates that this item is a valid indicator of teacher commitment to implement various evidence-based programs, regarding construct validity and convergent validity with other measures of commitment and with commitment predictors [22]. Teachers in the intervention group are also asked whether they liked the training, whether they found it useful, whether they found the content of the program useful, whether they liked the content of the program, and whether their students liked the content of the program. These items are rated on a 5-point Likert scale (from 1= “strongly disagree” to 5 = “strongly agree”). *Commitment score*: We will construct a standardized commitment score based on these previous items. Higher score indicates higher commitment to implement. As the psychometric properties of this score have not been validated, we will check the internal validity of the constructed score using Cronbach’s Alpha.*Preschool and kindergarten behavior scale (PKBS)- Social skills:* The PKBS social skills [54] is a teacher-rated scale assessing preschool and kindergarten children’s social skills. The French version of the scale is divided into 5 subscales [20]: The first subscale, “social interaction’ consists of 10 items that reflect behaviors and attitudes necessary to develop and maintain good relationships and friendship with others (such as defend others’ rights, helping others), “participates in classroom or family discussions,” “shows affection for other children,” or “tries to understand another child’s behavior.” The second subscale consists of six items and reflects components of “agreeableness with peers,” such as “plays with several different children,” “makes friend easily,” or “smiles and laughs with other children.” The third subscale, “compliance,” relates to respect for adult authority and social norms, such as “follows instructions from adults,” “follows rules,” or “uses free time in an acceptable way.” The fourth subscale, “cooperation with peers,” describes behaviors such as “shares toys and other belongings” or “gives in or compromises with peers when appropriate.” Finally, the fifth factor, labeled “autonomy,” is composed of items such as “works or plays independently,” “adapts well to different environments,” or “attempts new tasks before asking for help.” *Total PKBS Social Skills Score, PKBS Social interaction score, PKBS Agreeableness with peers score, PKBS Compliance score, PKBS Cooperation with peers scores, PKBS Autonomy score; PKBS functional level categorical score*: The 34 items are rated on a 4-point Likert scale ranging from 0 (= Never) to 3 (= Often). Total raw scores and raw scores for each subscale are calculated by adding scores of each item, with higher scores indicating better social skills. For 5–6-year-old children, total raw scores are divided into 4 functional level categories based on child age: “high functioning” (scores 95 to 102), “average” (scores 76 to 94), “moderate deficit” (scores 59 to 75), and “significant deficit” (scores 0 to 58) to compute a functional level categorical variable.*Strengths and difficulties questionnaire (SDQ)-extended teacher version*: The SDQ-extended teacher version is a scale used to measure children’s externalized symptoms, internalized symptoms, and pro-social behaviors [42]. It is divided into five factors of five items each: emotional symptoms, conduct problems, hyperactivity-inattention, peer problems, and prosocial behavior. At the end of the questionnaire, 4 items explore impacts of difficulties (overall distress, social impairment, learning impairment, and burden for teacher and classroom) [41]. The SDQ displays satisfactory reliability and validity [42] and although its factor structure in French language remains uncertain [15, 16], the SDQ French version shows satisfactory reliability and content validity for the total difficulties score [16]. *SDQ total difficulties score, SDQ impact score*: The 25 items are statements rated on a 3-point Likert scale indicating to what extent each statement applies to a target child, with 0 = Not true, 1 = Somewhat true, 2 = Certainly true. All factors except Prosocial behavior are summed in a Total difficulties score. Items relative to impact of difficulties are coded from 0 to 2, with 0 corresponding to no impact or little impact, 1 corresponding to “Somewhat impactful”, and 2 to “Very impactful”. An impact total score ranging from 0 to 8 is then generated by summing these items. Higher scores indicate higher levels of difficulties and higher level of impact.*Student-teacher relationship scale-short form (STRS):* The STRS-short form is a teacher-rated scale exploring teachers’ perspective on their relationship with a designed child in their classroom [60]. The scale comprises two distinct factors, one measuring the degree to which teacher-child relationship is characterized by warmth, positive emotions and open communication (closeness), and the other measuring the degree to which the relationship is characterized by negative emotions and interactions (conflict). This scale possesses excellent psychometric properties across multiple samples [60]. The validation of the French version is ongoing [21]. *STRS Closeness score, STRS Conflict score:* The 15 items (8 items assessing Closeness, 7 items assessing Conflict) are scored using a 5-point Likert scale ranging from 1 (= Definitely does not apply) to 5 (= definitely applies). Total scores are then calculated for each factor.Teacher personal well-being P-WB:*Comprehensive inventory of mindfulness experience (CHIME):* The Comprehensive Inventory of Mindfulness Experience (CHIME) is a self-report multidimensional scale measuring “dispositional” (or “trait”) mindfulness in adults with or without knowledge or previous contact with mindfulness [9, 53]. It captures the following eight dimensions of “trait” mindfulness: awareness of internal experience, awareness of external experience, acting aware, self-acceptance and non-judgment, non-reactivity, openness and non-avoidance, ability to relativize, and insight. The CHIME exhibited good reliability and satisfactory construct validity [9]. The validated French version of the scale used in this study showed highly satisfactory psychometric properties as well [71]. *CHIME Total score:* The 37 items are rated on a 6-point Likert scale (from 1 = “fully applies” to 6 “does not apply at all”). Total score is calculated by inverting each item score and adding all inverted score. Higher scores indicate higher proneness to experience mindfulness in everyday life.*Warwick-Edinburgh mental well-being scale (WEMWBS):* The Warwick-Edinburgh mental well-being scale (WEMWBS) is self-report single-factor measure composed of positively worded items related to positive mental health and well-being [74]. It covers a wide-range of concepts associated with positive mental health, including hedonic and eudemonic well-being, satisfying personal relationship, and positive functioning. The original version displayed good content validity and reliability [74], and the French version used in this study showed good internal consistency, stability and construct validity [77]. *WEMWBS Total score*: The 14 items are rated on a 5-point Likert scale (from 1= “never” to 5 = “always”), with high score indicating higher mental well-being.*Satisfaction with professional life scale (Echelle de Satisfaction de Vie Professionnelle; ESVP):* The ESVP scale is a unidimensional French short self-report measure of general professional life satisfaction derived from the Satisfaction with Life scale from Diener et al. (1985) [29, 39]. It displays adequate level of internal consistency and temporal stability, and good construct validity [39]. *ESVP total score*: The 5 items are rated on a 7-point Likert scale (from 1= “strongly disagree” to 7 = “strongly agree”), with higher scores indicating higher professional life satisfaction.

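### The reporting rule admits adverse events only when they are directly related to the intervention, so the published events cannot be compared between arms

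*Protocol article*

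**What the plan says.** The Protocol article deals with harms in one short section, Adverse event reporting and harms {22}. It has three parts:

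- An expectation: "Due to the intervention nature, serious adverse events are not expected".
- A reporting rule: any adverse event "will be reported in the manuscript describing trial results if they are directly related to intervention".
- A handling rule: "Those adverse events will be monitored by principal investigators and addressed until resolution".

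Under Composition of the data monitoring committee {21a} it adds: "An independent data monitoring committee has not been formed and no independent auditing will take place". Implementation {16c} says that one of the principal investigators "generated the allocation sequence, enrolled teachers, and assigned teachers to interventions". Intervention description {11a} lists the same investigator among those who give the two-day training to intervention teachers.

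**The concern.** Relatedness is used here as a condition for publication, not as a description of an event. In a randomised trial the fair evidence on harm is the contrast between arms: events are counted in the same way in both, and randomisation accounts for the background rate. A relatedness filter replaces that contrast with case-by-case opinion, and the opinion can apply to one arm only. A reader of the results paper would see a list of intervention-arm events, or an empty list, with nothing to set beside it.

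The article also leaves open who gives the opinion. The only people named in the section are the principal investigators, and at least one of them knows the allocation and has a part in delivering the teacher training.

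**Working it through.** There is no figure to reproduce. The article gives no adverse event rate, and the point depends on no power, effect size or sample size. The check is to read the rule against the sections that determine who can satisfy it.

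1. **Condition for publication.** Under {22}, an event must be directly related to the intervention.

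2. **Who is exposed.** Trial design {8} gives 32 classrooms per arm. Under Intervention description {11a}, control teachers continue their normal activities. Explanation for the choice of comparators {6b} offers them the training only in the following school year. During the evaluation year a control child therefore has no programme exposure to which an event could be related.

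3. **Consequence.** Let r0 be the true event rate in control classes and q0 the share of those events that can be judged directly related. The published control rate is r0 × q0. With q0 at or near 0, the product is at or near 0 for every value of r0. In the intervention arm the published rate is r1 × q1, where q1 is set by opinion. The published figures contain no information on r1 − r0 or on r1/r0.

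4. **Why q0 is near zero and not exactly zero.** Control teachers may take the training in the second year, and 28 of the 64 classrooms mix pre-K and kindergarten levels. A control child who stayed with the same teacher might then meet the programme. The article does not say how often this happens, and it would not make the two arms comparable.

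5. **Who could judge relatedness.** Section {22} says only that the principal investigators monitor events. Who will be blinded {17a} states that the investigators in charge of analysis are blinded, and one of these is also a principal investigator. Procedure for unblinding {17b} says that none was prepared. Deciding whether an event is related to the programme normally requires knowing whether the class received it. The principal investigator who made the allocation is the one clearly in a position to do so. This is an inference; the article does not state it.

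6. **Any other route.** Dissemination plans {31a} promises submission of all relevant results whatever their direction, but does not mention adverse events or lift the condition in {22}. Frequency and plans for auditing {23} accepts a regulatory audit and leaves the reporting rule as it is.

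**The case against.** **The rule may be only a minimum.** The sentence in {22} says that related events will be reported; it does not say in words that others will not be. That is fair as grammar. But it is the only commitment in the article, and an author who follows it to the letter would publish nothing from the control arm.

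**A fuller document may hold the detail.** A journal article condenses, and recording procedures may well be described elsewhere. That excuses missing detail, but not a rule that is stated and would give one-sided data if followed.

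**Worsening can be seen in the outcomes.** SDQ total difficulties and impact, STRS conflict and InCLASS negative classroom engagement are collected in both arms, and the subgroup analyses include children's initial problem behaviours. This stands in part: these outcomes can show a harmful shift, and the InCLASS observers are blinded. They are analysed as efficacy outcomes, however, and do not replace a count of events.

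**Stronger readings that the article does not support.**

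- A reader might infer that the plan hands attribution to an unblinded judge. The article does not say who judges. The inference is plausible, but it remains an inference.
- A reader might infer that the trial is set up to claim absence of harm. No such claim is planned; {22} says only that serious events are not expected.
- A reader might infer that the plan is wrong not to tabulate children who worsen on the SDQ by some threshold. That is an optional preference. The SDQ is rated by teachers who know their allocation, so such a table would also rest on unblinded judgement.

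**Conclusion.** The concern holds in a narrow form. As written, the rule makes published adverse events depend on direct relatedness, a condition that control-arm events can hardly ever meet, so the published events cannot be compared between arms. This follows from {22} read with {11a} and needs no assumption about event rates.

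The numerical effect cannot be given, because the article states no event rate for either arm. The importance is modest: the investigators expect no serious events, and the estimates for the primary and secondary outcomes do not change. What would be lost is the ability to interpret whatever the results paper says about adverse events. The absence of an independent committee and the unstated judge of relatedness add to the reason for dropping the filter, but the conclusion does not rest on them.

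**What to change.** Reword {22} so that all recorded adverse events are reported by arm, with relatedness given as a descriptive column and no longer as a condition. Say who assigns relatedness and whether that person knows the allocation.

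Ask about events in the same way in both arms. Relevant concomitant care {11d} already puts questions to all teachers, intervention and control, at the end of the first and second years; one question on adverse events could be added there. This matters because the implementation notebooks are kept only by intervention teachers and the personal contacts described in the Discussion serve to monitor programme implementation. Events picked up through those channels would come mainly from one arm. State any remaining difference in how events were ascertained, and if the first-year questions have already been put, say that the information was collected in retrospect.

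The cost is one added question and one added table. The small downside is that some background events unrelated to the programme will be listed.
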